##### Mathematical statistics analysis and expression

• Comparison between groups: The chi-square test for enumeration data; Wilcoxon rank sum test for non-normal distribution of measurement data; t-test for normal distribution of measurement data; ANOVA for repeated measurement data; Ridit test for ranked data; CMH test for the center effect.

• Dropping analysis: The chi-square test, or Fisher exact probability method.

• Compliance analysis: The chi-square test, or Fisher exact probability method.

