## Background

An increasing number of people experience complications from symptoms of pre-diabetes. Some studies have discovered that about 5%-10% of pre-diabetes will develop into diabetes within one year and the occurrence of cardiovascular events in patients with pre-diabetes are higher than in healthy individual. According to Hoorn[1], the rates of development of diabetes after 5.8-6.5 years follow-up from patients with normal glucose tolerance, single impaired fasting glucose (IFG), single Impaired Glucose Tolerance (IGT), both IGT and IFG people are 4.5%, 33.0%, 33.8% and 64.5%, respectively. Therefore, the prevention of type 2 diabetes in pre-diabetic patients is a topic of importance in diabetes research.

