### Randomization

The randomization of the trial will be completed by the independent data center named Interact Voice Responding System (IVRS). According to a random sequence table (generated by SAS8.2), participants who satisfied the inclusion criteria will be allocated randomly into one of the two groups with a ratio of 1:1. The identification code and random number, which is unique for each participants, will be generated by the IVRS.

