### Sample size

According to the results of the "JQJT tablets intervene IGT study" by Professional Committee of Diabetes, Association of Integrative Medicine in Tianjin, annual average tyoe 2 diabetes conversion rate of test group is 4.05%, control group is 12.69%. The sample was estimated according to the parameters: *α *= 0.05, *β *= 0.1

Considering attrition of no more than 20%, the total number of qualified cases in the groups will be 200 each (n = 400).

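### The continuous primary outcomes (OGTT, insulin release, HbA1c) are compared without a baseline covariate, although screening values are collected; ANCOVA or a mixed model would be more precise at no extra data cost

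*Protocol article*

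**What the plan says.** The section on mathematical statistics analysis assigns each between-group test by type of data. Measurements get "t-test for normal distribution of measurement data; ANOVA for repeated measurement data", or a Wilcoxon rank sum test if not normally distributed. Neither this section nor the preceding one on analysis sets names ANCOVA, a baseline covariate or a change from baseline for any measured outcome.

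The Primary outcomes section lists the oral glucose tolerance test, the insulin releasing test and HbA1c. All three are continuous. Tables 1 and 2 schedule them as follows:

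- **OGTT:** screening, every month from 1 to 12, then months 14, 18 and 24.
- **Insulin release and HbA1c:** screening, month 12 and month 24.

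The article does not say whether the t-tests use follow-up values or changes. Nor does it say whether the repeated-measures ANOVA takes screening as one of its time levels.

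**The concern.** A person's screening glucose, insulin or HbA1c usually predicts the later value of the same measure. A test that ignores it leaves that between-person variation in the error term. A test on the change from screening uses it, but subtracts it with a fixed weight of one, which is generally not the best weight. Regressing the follow-up value on the screening value lets the data set the weight.

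At stake is the width of the confidence intervals on all three primary outcomes, and how far the estimates move when the arms differ by chance at screening. The screening values are in the visit schedule already, so the information is paid for whether or not the analysis uses it.

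**Working it through.** **No plan figure to reproduce.** The Sample size section rests on diabetes conversion alone ("conversion rate of test group is 4.05%, control group is 12.69" percent). The article gives no standard deviation, target difference or power for OGTT, insulin or HbA1c. The check is therefore on relative precision.

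**Inputs**

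- 200 per arm and at most 20% attrition (Sample size section): 200 × 0.8 = 160 completers per arm.
- r, the correlation between screening and follow-up value: not in the article. Assumed 0.3, 0.5 and 0.7.
- Reference power of 80% at two-sided 5%: an illustration, not a plan figure. The standardised effect is 1.96 + 0.84 = 2.80.

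**Formulas**, with s0 and s1 the standard deviations at screening and follow-up. Variances are per person:

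- final-value t-test: s1²
- change-score t-test: s0² + s1² − 2·r·s0·s1, which is 2(1 − r)·s1² if s0 = s1
- ANCOVA: s1²(1 − r²)

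So ANCOVA against final values has the variance ratio 1 − r². Against change, with s0 = s1, the ratio is (1 − r²)/[2(1 − r)] = (1 + r)/2. Power that starts at 80% becomes Φ(2.80/√ratio − 1.96).

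| r | Ratio to final values | 160 per arm act like | 80% power becomes | Ratio to change score |
|---|---|---|---|---|
| 0.3 | 1 − 0.09 = 0.91 | 160/0.91 = 176 | 83.6% | 1.3/2 = 0.65 |
| 0.5 | 1 − 0.25 = 0.75 | 160/0.75 = 213 | 89.9% | 1.5/2 = 0.75 |
| 0.7 | 1 − 0.49 = 0.51 | 160/0.51 = 314 | 97.5% | 1.7/2 = 0.85 |

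**Does the direction depend on r?** No. The ratio 1 − r² never exceeds 1. The change-score variance minus the ANCOVA variance equals (s0 − r·s1)², which is never negative, whether or not the two standard deviations are equal. In large samples ANCOVA is therefore at least as precise as either alternative.

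**Does the size depend on it?** Yes. The two comparators also move in opposite directions: a higher r raises the gain over final values and lowers the gain over change.

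**The case against.** **Screening may already be used.** All three outcomes are measured repeatedly, so the ANOVA in the quoted clause may be the intended method, with screening as a time level. Its group-by-time term would then work like a comparison of changes. This stands: the article does not establish that screening values are ignored, and the 9% to 49% range applies only if final values are compared. A change-type comparison is still no more precise than ANCOVA.

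**The correlation is assumed.** The entry windows for fasting and 2-hour glucose narrow the spread at screening, which tends to lower r. That is why the range starts at 0.3, where the gain over final values is only 9%. If the windows also make s0 smaller than s1, the gain over change shrinks too, and it vanishes at s0 = r·s1. Where the plan would use a Wilcoxon test, these factors do not apply directly.

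**The planned tests are valid.** This is correct. Under randomisation, chance imbalance is covered by the confidence interval and is not bias. The point concerns efficiency only.

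A reader might also infer four stronger points. The document does not support them.

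- *Conversion is tested only by a crude chi-square.* The article does give "The chi-square test for enumeration data", but the analysis-sets section also lists survival analysis and Cox regression. That Cox covariates are unnamed is detail an article may leave to a fuller document.
- *CMH is misused.* "CMH test for the center effect" stands in the same list of between-group comparisons. It can naturally be read as a centre-stratified comparison of treatments.
- *Adjusting conversion for IFG/IGT type would gain much precision.* The Background rates ("both IGT and IFG people are 4.5%, 33.0%, 33.8% and 64.5%, respectively") cover 5.8 to 6.5 years, against 12 months of intervention. Annualise them, scale them to the planning rates and assume that 30% of participants have both conditions. The risks are then about 8.9% and 21.5% on control and 2.8% and 6.9% on treatment. The summed risks differ by 0.284 − 0.117 = 0.167, and half their between-type variance is 0.5 × 0.7 × 0.3 × 0.167² = 0.0029. The binomial variances total 0.0405 × 0.9595 + 0.1269 × 0.8731 = 0.150. The factor is 1 − 0.0029/0.150 = 0.98, so 160 per arm act like about 163.
- *ANCOVA would repair a shortfall in the stated power.* The stated power concerns conversion only. ANCOVA on the continuous outcomes does not touch it.

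**Conclusion.** The point holds for OGTT, insulin release and HbA1c, and only there. The article fixes tests with no baseline covariate for its three primary outcomes while scheduling the covariate for each. The tests are sound but less precise than they could be.

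With r assumed between 0.3 and 0.7, the variance saved is 9% to 49% if the plan means final values. If it means changes, the saving is 35% at r = 0.3, falling to 15% at r = 0.7, given equal standard deviations. The direction is firm in large samples. The size is not, because the article gives neither r nor the comparator. This is a recommended improvement, not an error that would invalidate the trial's conclusions.

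**What to change.** In the section on mathematical statistics analysis, replace the t-test and ANOVA entry for the continuous primary outcomes with:

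1. **Insulin release and HbA1c, and OGTT at month 12:** ANCOVA of the month-12 value, with arm, the screening value of the same measure and centre. Report the adjusted difference with its 95% confidence interval.
2. **Monthly OGTT:** a mixed model for the post-screening visits, with the screening value and centre as covariates and visit-by-arm terms. State how it relates to the last-observation-carried-forward rule in the analysis-sets section, that is, whether it is fitted to observed or to filled-in visits.
3. **Skewed outcomes such as insulin:** a pre-specified transformation, or rank ANCOVA in place of the Wilcoxon test.

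The cost is wording only, to be settled before the group codes are released to the statisticians. No patient, visit or measurement is added. The few degrees of freedom spent on covariates are negligible with about 160 completers per arm.

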#### Documents conservation and summary

The documents such as informed consent, signature of participants and other cases are requested to conserve clearly according to GCP by every unit after the study. Researchers should preserve the material of clinical trial for five years.

#### Data management

##### Data input

Database manager designs EpiData3.1 database. The data manager carries on the test to the database base on analogue data or real CRF data. Data are inputted by two full time personnel independently.

##### Data verification

• Comparing with duplicate input result.

• Checking data uniformity and logic.

• Spot-checking 10% CRF, compare database with CRF form.

##### Data locked-up

The main data will be locked up until research completed. New question will carried on statistical analysis procedure after data locking; all contents and the revision should be preserved well. For the questions in the CRF, data manager should produce DQF and inquire the researchers through clinical supervisor. Data manager should make data modification, affirmation and record according to the reply of researchers.

#### Management of investigational drug

JQJT tablets and placebo are all supplied by Longshunrong Pharmaceutical Company in Tianjin. According to double-blind method, the packing of placebo should be consistent with the investigational drug. Researchers will be provided with the drug serial number and distribute drugs to participants monthly through 800 telephone terminals. The drug managers take charge of preservation of investigation agent. When adverse event happens, researchers can uncover blindness through the DSMB.

#### Trial management

##### Change of protocol

All changes of protocol should be preserved and any modification of the protocol, including ICF, must get the approval of ethics committee.

##### CRF tracking

All signed ICF must be handed over even if some of them are unqualified; any questions of CRF or comments must be submitted directly to the organizer.

##### Change of research center

The decision to change research center should be careful and these change must be reported to ethics committee. Research center would be changed for slow speed of study, severe violation of protocol and GCP.

#### Researcher's responsibility

Researcher must understand protocol details and adhere to it strictly. They should understand the related information of investigation agent, including function, curative effect and security. They should have enough time to complete this study on schedule and have responsibility to explain study process and consent form to participants. Participants with adverse events should be treated suitably and related data should be recorded accurately and completely in primitive medical record and CRF. Researcher should accept censorship or examination from organizer of clinical trial or other inspected departments.

#### Quality control

##### Quality control of laboratory

• All hospitals should establish uniform SOP and quality control sequence.

• All units should offer researcher suitable medical equipments and emergency facilities.

• Certain item should be in charged by special personal.

##### Request for researcher

Researchers in this study must possess the qualifications and ability to carry on it and they should not be changed constantly.

##### Measures for compliance of participants

Researchers should give investigational drug to in-patient in time and explain medication method to outpatient. Compliance of participants will be inspected by method of drug notation. They are asked to bring drug last time in order to calculate the number.

##### Monitoring and inspection

Monitor should constantly visit each unit to know the situation of facility and research follow, reexamine CRF, check storage of investigational drug and record of data.

According to GCP, organizer will carry on conventional and emphasis inspection on related activities and documents of every unit during study in order to evaluate whether the process of study is in accord with protocol and standard practice, whether collected data are recorded prompt, accurate and completely.

##### Bias control

Any other west or TCM drugs which has similar effects as the investigated agent will be prohibited when participants decide to participate this study. Researcher should pay close attention to contamination and disturbance in this study in order to prevent occurrence of bias.

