##### Suspension criteria

• Poor compliance.

• Serious adverse events, complications and special physiological changes.

• Unblinded abnormally.

• Reluctance to continue this study.

• Taking medicine forbidding in this study.

• Withdraw for various reasons, such as failure to follow up or death.

• Incomplete information which will influence the study.

• Big mistake in protocol or significant deviation in implement (such as the leak of blind).

• National laws, ministry of science and technology or other authorities decided to terminate the study.

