##### Contents

Data should be captured according table 1 and 2.

**Table 1 T1:** Content of data capture(to be continued)

Item	Screening period (unit: month)	Intervention period (unit: month)											
	
	-0.5	1	2	3	4	5	6	7	8	9	10	11	12
ICF	X												

Record of medical history	X												

Demographic information	X												

General physical examination	X	X	X	X	X	X	X	X	X	X	X	X	X

FBG	X	X	X	X	X	X	X	X	X	X	X	X	X

PBG	X	X	X	X	X	X	X	X	X	X	X	X	X

OGTT	X	X	X	X	X	X	X	X	X	X	X	X	X

Insulin release test	X												X

HbA1c	X												X

serum TC, LDL-C, VLDL-C	X												X

Blood and urine regulation	X						X						X

ALT, AST	X			X			X			X			X

BUN, Cr	X			X			X			X			X

Electrocardiogram	X												

Pregnancy Test	X						X						X

Selection/exclusion criteria	X												

Drugs of prohibition	X												

SF-36	X												X

Evaluation of TCM Syndrome	X												X

Obtain random code	X												

Dial 800 to Assign drug	X			X			X			X			

Drug Distribution and record	X	X	X	X	X	X	X	X	X	X	X	X	

End-point events		X	X	X	X	X	X	X	X	X	X	X	X

Adverse events	X	X	X	X	X	X	X	X	X	X	X	X	X

Drug combination		X	X	X	X	X	X	X	X	X	X	X	X

X: Item need to be done during different period.

**Table 2 T2:** Content of data capture

Item	Period after intervention (unit: month)		
	
	14	18	24
General physical examination	X	X	X

FBG	X	X	X

PBG	X	X	X

OGTT	X	X	X

Insulin release test			X

HbA1c			X

Serum TC, LDL-C, VLDL-C			X

ECG			X

Blood and urine regulation			X

ALT, AST, BUN			X

SF-36			X

Evaluation of TCM Syndrome			X

Pregnancy test		X	X

End-point events	X	X	X

Adverse events	X	X	X

Drug combination	X	X	X

X: Item need to be done during different period.

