#### Outcome measures

##### Index of end point

• Occurrence of type 2 diabetes (according to the guideline of ADA 2008);

• Blood glucose change to be normal.(FPG<5.6 mmol/L & OGTT 2 hPG <7.8 mmol/L)

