##### Primary outcomes

• Oral glucose tolerance test

• Insulin releasing test

• Glycosylated hemoglobin (HA1c)

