##### Analysis of data sets

• Full analysis set: According to the principle of analysis for intention to treat (ITT), participants will be rejected by smallest and reasonable method. The last observation carried forward (LOCF) method will be used for the missing data supplement.

• Per-protocol set (PPS): PPS should be used in the patients who satisfied with the following characters: compliance is between 80% and 120%; not using prohibited drugs; fit with inclusion criteria; case of completed observation.

• Safety set (SS): All information of safety record will be assessed, including adverse events and laboratory test results.

• Statistical analysis method: Relative risk reduction (RRR), absolute risk reduction (ARR), number needed to treat (NNT) adopt nonparametric methods to evaluate the effectiveness. To adopt t-test, repeated measure analysis of variance, radit test, rank test, survival analysis, Cox proportional hazards regression model and so on.

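### A participant treated for diabetes after reaching the end point becomes a prohibited-drug user and leaves the per-protocol set because of the outcome

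*Protocol article*

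**What the plan says.** Five parts of the protocol article bear on this.

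- **The ban.** The Bias control section, under Quality control, states: "Any other west or TCM drugs which has similar effects as the investigated agent will be prohibited when participants decide to participate this study". No end date is given, and no exception after an end-point event. The section on the tablets' constituents describes some of them as lowering blood sugar, so ordinary glucose-lowering drugs are the natural reading of a similar effect.
- **The sanction.** Suspension criteria lists "Taking medicine forbidding in this study" as a ground, again without exception.
- **The per-protocol set.** Analysis of data sets requires compliance of 80% to 120% and then "not using prohibited drugs; fit with inclusion criteria; case of completed observation". The full analysis set follows the intention-to-treat principle and has no prohibited-drug condition.
- **The end point.** Index of end point names "Occurrence of type 2 diabetes (according to the guideline of ADA 2008"), alongside return to normal glucose. Tables 1 and 2 record end-point events and concomitant drugs at every visit after screening, through month 24.
- **The effect measures.** Analysis of data sets states: "Relative risk reduction (RRR), absolute risk reduction (ARR), number needed to treat (NNT) adopt nonparametric methods to evaluate the effectiveness". Survival analysis and Cox regression are also listed.

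**The concern.** A per-protocol set should exclude people for departing from the protocol, not for having the outcome. Here the usual response to the outcome, starting a glucose-lowering drug, counts as a departure. Everyone removed by this route is a converter, so each exclusion deletes an event. If JQJT works there are more converters on placebo, and so more deletions there.

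What is at stake is the per-protocol analysis of conversion, in particular its absolute measures. An analysis that has discarded events because they occurred cannot serve as a check on the absolute benefit seen in the full analysis set.

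**Working it through.** **Inputs from the Sample size section.** Annual conversion is 4.05% on JQJT (p₁) and 12.69% on control (p₂), with 200 randomised per arm and attrition of no more than 20%.

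**Input not in the documents.** Let f be the share of converters who are given a glucose-lowering drug and excluded. The range 0% to 100% is shown. It is taken as equal in both arms, which is reasonable under double blinding.

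**The plan's own figure.** The stated 200 per arm cannot be firmly reproduced. A two-sided pooled comparison of proportions with 90% power needs 214 per arm before attrition and 268 after. Only a one-sided arcsine version comes within 3% of 200 (205 dividing by 0.8, 197 multiplying by 1.2), and sidedness is not stated. Nothing below depends on this. The planned effect is 12.69 − 4.05 = 8.64 points, so NNT = 1/0.0864 = 11.6, and the risk ratio is 4.05/12.69 = 0.319.

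**Expected year-1 conversions.** Without attrition: 200 × 0.1269 = 25.4 and 200 × 0.0405 = 8.1, total 33.5. With 20% loss: 160 × 0.1269 = 20.3 and 160 × 0.0405 = 6.5, total 26.8. These are upper bounds on year-1 exclusions by this route, reached only if every converter is treated.

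**Per-protocol rate.** Removing a share f of converters takes them out of both numerator and denominator:

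rate = p(1 − f) / (1 − pf)

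The arm size cancels, so attrition unrelated to outcome does not change the rates.

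| f | Control | JQJT | ARR (points) | NNT | Risk ratio |
|---|---|---|---|---|---|
| 0% | 12.69% | 4.05% | 8.64 | 11.6 | 0.319 |
| 25% | 9.83% | 3.07% | 6.76 | 14.8 | 0.312 |
| 50% | 6.77% | 2.07% | 4.71 | 21.2 | 0.305 |
| 75% | 3.51% | 1.04% | 2.46 | 40.6 | 0.298 |
| 100% | 0% | 0% | 0 | – | – |

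Example at f = 50%: control 0.1269 × 0.5 / (1 − 0.06345) = 0.0677; JQJT 0.0405 × 0.5 / (1 − 0.02025) = 0.0207; difference 0.0471.

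**Why the risk ratio holds.** It equals (p₁/p₂) × (1 − p₂f)/(1 − p₁f). With both rates small the second factor stays near 1; at f = 75% it is 0.9048/0.9696 = 0.933.

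**Precision.** Starting from 160 evaluable per arm, two-sided power for the per-protocol comparison is about 80% at f = 0, then about 69%, 52% and 30% at f = 25%, 50% and 75%.

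**The case against.** The strongest reply has four parts.

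1. **The article is condensed.** A fuller protocol or analysis plan may hold the exception. That is possible. But the article itself states the ban, the suspension ground and the per-protocol conditions, and followed as written they produce the exclusion. The fault is in rules that are stated, not in detail left out.
2. **The ban may apply only at entry.** Its wording is tied to the decision to take part, and Table 1 ticks prohibited drugs only at screening. This does not hold, because Suspension criteria and the per-protocol definition both apply the ban during the study.
3. **No per-protocol conversion analysis is stated, and survival methods are listed.** The first half stands: such an analysis is implied by defining the set and naming ARR and NNT, but it is not spelled out. Survival methods do not help, since a participant excluded from the set takes the event along whatever model is used.
4. **The harm is limited.** This stands. The relative effect is nearly unchanged, the absolute effect moves toward zero and so cannot create a false benefit, and the share treated is assumed.

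A reader might also infer more than the text supports:

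- **That converters are denied treatment.** The duty of suitable care under Researcher's responsibility and the Helsinki commitment leave a route to care.
- **That the main incidence result is biased.** Conversion is recorded before treatment starts, and the full analysis set has no prohibited-drug condition.
- **That primary outcomes are damaged through imputation.** The argument is that "The last observation carried forward (LOCF) method will be used for the missing data supplement", while "Glycosylated hemoglobin (HA1c") and the "Insulin release test" are scheduled only at screening and months 12 and 24, so baseline values would be carried forward for early converters. This needs suspension to end visits, which is not stated. The fix would observe HbA1c under treatment, so the untreated rise in converters is the wrong measure of the loss. The glucose tolerance test is monthly, so a post-conversion value could be carried forward. It is a minor conditional note, and no size is claimed for it.

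**Conclusion.** The concern holds for the per-protocol set. A converter who starts a glucose-lowering drug meets a suspension criterion and fails the per-protocol definition because of the outcome. At the planning rates, with 25% to 75% of converters treated and excluded, the per-protocol ARR falls from 8.6 points to between 6.8 and 2.5, and the NNT rises from 12 to between 15 and 41. With all converters treated, no comparison of incidence remains.

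This rests on three assumptions: that glucose-lowering drugs fall under the ban, that some converters receive them (share not given, taken as equal between arms), and that conversion is analysed in the per-protocol set. The risk ratio moves only from 0.32 to 0.30 over that range, and the full-set conversion comparison is intact. It is worth fixing because the remedy is so cheap, but it does not threaten the trial's main incidence result.

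**What to change.** - **Bias control:** end the ban on similar-effect drugs, for that participant, at a recorded diabetes end-point event.
- **Suspension criteria and the per-protocol definition:** state that glucose-lowering treatment started after that event is neither a ground for suspension nor a reason for exclusion, and that the participant stays in scheduled visits to month 24.
- **Data handling:** flag glucose, insulin and HbA1c values after the treatment start as on-treatment, using the existing drug-combination record in Tables 1 and 2.

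The cost is two or three amendment sentences and ethics committee approval, with no new visits, tests or forms. The small downside is that later glucose, insulin and HbA1c values in treated converters reflect that treatment and must be read with the flag.
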